# Efficacy of Tuina Versus the Proprioceptive Neuromuscular Facilitation (PNF) Technique in Patients With Nonspecific Chronic Neck Pain: Protocol for a Randomized Controlled Trial

**DOI:** 10.2196/63528

**Published:** 2025-08-14

**Keywords:** nonspecific neck pain, nonspecific chronic neck pain, efficacy, randomized controlled trial, tuina, proprioceptive neuromuscular facilitation, combined therapy, neck pain, chronic neck pain, evidence, support, effectiveness, therapy, China, manipulation, traction, cervical traction

## Abstract

**Background:**

Nonspecific chronic neck pain (NCNP), characterized by a long course, a high recurrence rate, and a young age of onset, causes a huge economic burden. Scientific evidence supports the efficacy of tuina, a manual traditional Chinese medicine (TCM) therapy involving manipulation of soft tissues and joints, for NCNP. However, there is little evidence of the effectiveness of proprioceptive neuromuscular facilitation (PNF), a rehabilitative method involving specific patterns of muscle contraction and stretching, in treating NCNP, either alone or in combination with tuina.

**Objective:**

This study aims to compare the effects of the PNF technique, tuina, and their combination on patients with NCNP and assess whether combined therapy outperforms monotherapies.

**Methods:**

The parallel, double-blind, three-arm clinical randomized controlled trial (RCT) is being conducted at the Beijing University of Chinese Medicine and its affiliated hospitals. Patients will be recruited and randomly assigned to a PNF group, a tuina group, and a combined (PNF+tuina) group in a 1:1:1 ratio. The PNF intervention (PNF stretching and PNF plyometrics) will last for 30 minutes each session. Tuina therapy will also last for 30 minutes each session. The combined group will receive 30 minutes of PNF, followed by 30 minutes of tuina therapy. Participants will receive 4 weeks of treatment, thrice a week, for a total of 12 treatments. Visual Analogue Scale (VAS) and Neck Disability Index (NDI) scores will be used as primary outcome measures. Cervical active joint mobility measured with the MicroFET3 Portable Muscle Strength Test and Joint Mobility Meter and muscle physical properties tested with the Myoton Muscle Tester will be used as secondary outcome measures. Data will be analyzed at baseline, at the end of the intervention, and during the 4 weeks of follow-up using repeated measures ANOVA. The significance level will be 5%.

**Results:**

As of May 26, 2025, 43 participants were already recruited and randomly assigned to the three treatment groups (PNF: n=14, 32.6%; tuina: n=15, 34.9%; combined: n=14, 32.5%). All enrolled participants have initiated treatment, with an average adherence rate of 92% and no withdrawals due to adverse events (AEs) or treatment dissatisfaction. The short-term follow-up (end of intervention) for the first cohort was completed on July 30, 2025, with long-term follow-up (1 month postintervention) to be completed by August 31, 2025. The final analysis is projected to include data of all 69 participants by October 2025, with primary results expected to be submitted for publication in December 2025.

**Conclusions:**

Our findings will provide a solid evidence base for clinical approaches to managing NCNP. Moreover, our results will offer valuable insights into the relative efficacy of tuina, PNF, and their combination, shedding light on their potential benefits and helping identify the most effective treatment strategies for NCNP.

**Trial Registration:**

International Traditional Medicine Clinical Trial Registry ITMCTR2023000061; https://itmctr.ccebtcm.org.cn/mgt/project/view/346154483678331720/false

**International Registered Report Identifier (IRRID):**

PRR1-10.2196/63528

## Introduction

Nonspecific chronic neck pain (NCNP) is pain located in the lateral and posterior neck without a clear pathological cause (eg, a specific condition, such as a fracture, inflammation, or nerve compression) and often manifests itself as soreness, stiffness, or limitation of movement of the neck muscles [1]. When the duration of symptoms is greater than 12 weeks of evolution, it acquires the value of chronicity, being referred to as denominated NCNP [2]. It is a general term used to describe neck pain where no discernible histopathological structural abnormalities can be identified clinically [3,4]. In China, its annual incidence ranges from 43% to 66.7% [5], causing a huge economic burden [6,7]. The disease is characterized by a long course, a high recurrence rate, and a young age of onset.

The intrinsic mechanisms underlying the maintenance, recurrence, and progression of NCNP are unknown but may be related to deficits and alterations in neck muscle proprioception. This is because neck muscle proprioception plays a decisive role in cervical joint position and head movement control [5]. Due to the lack of identifiable pathological processes or specific etiologies in NCNP, it is difficult to implement precise treatment strategies [8].

Although pharmacological interventions, intra-articular injections, and surgical procedures are commonly used in clinical practice, their effectiveness is not guaranteed [9]. Current Western medical approaches, including nonsteroidal anti-inflammatory drugs and physical therapy, often provide short-term relief but show limited long-term efficacy due to high recurrence rates [10]. As a result, nonpharmacological approaches have gained increasing attention, with exercise therapy considered an effective method for pain relief [11].

In traditional Chinese medicine (TCM), *tuina*—manual therapy involving rhythmic pressure, kneading, and joint mobilization—has been used for millennia to alleviate neck pain by stimulating meridian points and releasing muscular tension. Tuina aims to regulate the flow of *Qi* (life force) and blood, relieve muscle tension, and promote blood circulation, thereby alleviating neck pain and improving functional impairments. Recent studies have demonstrated that tuina can significantly relieve symptoms of NCNP [12]. A systematic review of 12 RCTs (N=897 patients) found that tuina significantly reduced NCNP severity (mean Visual Analogue Scale [VAS] score reduction: 2.1 points) and disability (Neck Disability Index [NDI] reduction: 9.2 points) compared to sham treatments. Modern mechanistic studies suggest that tuina reduces pain by inhibiting pro-inflammatory cytokines and enhancing central pain modulation [8].

Proprioceptive neuromuscular facilitation (PNF), a rehabilitation technique developed in the 1940s, uses specific patterns of resisted muscle contraction and stretching (eg, the contract-relax method) to improve neuromuscular coordination and joint mobility. Although PNF has demonstrated efficacy in managing low back pain and shoulder stiffness, its application in NCNP remains understudied. Only two small trials (N=45 and N=60 patients, respectively) have explored PNF for neck pain, reporting modest improvements in the range of motion but no comparison with established therapies, such as tuina [13,14]. Critically, no study has directly compared tuina and PNF or investigated their combined use, leaving a significant gap in understanding whether their mechanisms—TCM’s holistic soft-tissue release and PNF’s neurophysiological modulation—might synergize to enhance outcomes.

In recent years, studies have confirmed that combination therapies are superior to monotherapies and have better long-term effectiveness [15]. In the context of cervical muscle rehabilitation, tuina and PNF share biomechanical principles and are potentially complementary. Their combination may improve energy metabolism and blood circulation, while helping restore both the static and the dynamic balance of the cervical spine. This synergistic effect may correct biomechanical imbalances and enhance proprioceptive feedback. However, no relevant clinical trials have been conducted to investigate this combined approach.

The aim of this study is to compare the therapeutic effects of tuina, PNF, and their combination in the treatment of NCNP and whether the combination therapy of PNF and tuina has superior efficacy compared to either therapy alone in order to provide more clinical evidence for the treatment of NCNP. Against this backdrop, this study aims to address three critical research questions:

Does the PNF technique demonstrate superior efficacy compared to tuina in reducing pain and improving functional disability?Does the combination of PNF and tuina yield better outcomes than either monotherapy alone?Are there significant differences in cervical joint mobility and muscle physical properties (eg, stiffness, elasticity) across the three treatment groups?

The specific objectives are to (1) compare the short-term (end of intervention) and long-term (4-week follow-up) efficacy of PNF, tuina, and their combination in reducing pain (VAS score) and functional disability (NDI); (2) evaluate their effects on cervical active joint mobility and muscle physical properties; and (3) assess the safety and tolerability of all interventions. Guided by these objectives, the primary hypothesis is that the PNF-tuina combination will achieve greater reductions in pain and disability than monotherapies, while the secondary hypothesis posits that PNF will outperform tuina in improving cervical biomechanics. All interventions are hypothesized to be safe, with low rates of adverse events (AEs).

## Methods

### Study Design

This trial has been registered in the International Traditional Medicine Clinical Trial Registry (registration number: ITMCTR2023000061). The study is a parallel, double-blind, three-arm clinical randomized controlled trial (RCT) without a standard care control. A total of 102 eligible patients with NCNP will be recruited and then randomly assigned to a PNF group, a tuina group, and a combined (PNF+tuina) group in a 1:1:1 ratio.

This design is a parallel-group, active-comparator trial aiming to directly compare the efficacy of three commonly used interventions for NCNP—PNF, tuina, and their combination—given the absence of head-to-head comparative evidence in the literature. By excluding a standard care control group, the trial focuses on identifying the most effective modality among the tested active interventions rather than evaluating superiority over usual care [16].

The PNF group will undergo the PNF intervention, the tuina group will undergo a TCM intervention with tuina, and the combined group will receive PNF combined with tuina therapy. The intervention will last for 4 weeks for each of the three groups, thrice a week.

This frequency and duration will be carefully determined. A treatment frequency of thrice a week is supported by both previous studies and physiological mechanisms. Research on rehabilitation interventions for cervical spondylosis has shown that a frequency of three sessions per week can maintain a continuous therapeutic effect, promoting muscle repair and reducing inflammation [8]. Biologically, the human musculoskeletal system requires an appropriate interval between treatments to complete the repair and remodeling process; a higher frequency may cause excessive stress on the tissues, while a lower frequency may weaken the cumulative therapeutic effect [17]. The 4-week total treatment duration is based on the natural course of cervical spondylosis and the expected efficacy period. Clinical experience and preliminary data from our center indicate that significant improvements in symptoms, such as pain and limited mobility, can be observed within 4 weeks of continuous treatment. Additionally, a 4-week treatment cycle strikes a balance between achieving therapeutic goals and patient compliance, as longer treatment periods may lead to decreased adherence due to factors such as time constraints and economic burden.

The primary outcome measures of this trial are the VAS and NDI scores. The secondary outcome measures are cervical active joint mobility and muscle physical properties. The three groups will be tested before the intervention (baseline), at the fourth week of the intervention, and at the follow-up visit 4 weeks after the end of the intervention. The study design is illustrated in the flowchart in Figure 1.

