### Randomization

The randomization sequence will be generated by a random number generator (IBM SPSS Statistics version 27.0), which will be sent to a therapist in opaque envelopes numbered sequentially. The therapist will sequentially open the envelopes and allocate participants accordingly. Eligible patients will be randomized to the tuina group, the PNF group, or the combined group, with 23 patients in each group.

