### Blinding

Outcome assessors, data managers, and the statistician will be blinded in this trial and will not share study information with each other. To preserve masking, only the massage therapists will have access to treatment allocation. The patients will not know the group to which they belong before the intervention. The sequence of randomization will be hidden from both evaluators and patients, and this sequence will be kept by the main researcher throughout the study and will not be available to the rest of the participants involved in the trial.

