#### Outcome Measurements

Two self-report tools and two detectors will be used to measure the outcomes. The VAS and NDI scores will be used as the primary outcome measures. Cervical active joint mobility measured with the MicroFET3 Portable Muscle Strength Test and Joint Mobility Meter and muscle physical properties tested with the Myoton Muscle Tester will be used as secondary outcome measures. Pain, cervical active joint mobility, cervical spine dysfunction, and muscle physical property measurements will be performed during the first week (preintervention) and after 4 weeks’ treatment.

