### Limitations

Although this trial provides valuable insights, several limitations warrant discussion. First, the single-center design may limit generalizability, as participants are being recruited from a tertiary hospital in Beijing, potentially introducing selection bias toward patients with more severe symptoms. Second, the sample size (N=69) may lack sensitivity to identify small but clinically meaningful differences, particularly in subgroup analyses, and the short intervention period (4 weeks) and 1-month follow-up do not capture long-term outcomes, such as recurrence rates. Third, the inability to blind therapists to treatment allocation may have introduced performance bias, and limited use of objective measures (eg, surface electromyography) may hinder mechanistic insights. Despite these limitations, the trial supports exploring PNF as a stand-alone intervention and its integration with tuina, with future research recommended to adopt multicenter designs, extend follow-ups, and use of objective biomarkers.

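### The trial is labelled double-blind, but the plan does not blind participants or therapists during treatment, and both primary outcomes are participants' own reports

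*Protocol article*

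**What the plan says.** The label appears twice. The abstract's Methods paragraph reads "The parallel, double-blind, three-arm clinical randomized controlled trial (RCT) is being conducted", and Study Design repeats it: "The study is a parallel, double-blind, three-arm clinical randomized controlled trial (RCT) without a standard care control".

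The Blinding section then sets out who is masked:

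- Staff: "Outcome assessors, data managers, and the statistician will be blinded in this trial and will not share study information with each other".
- Therapists: "only the massage therapists will have access to treatment allocation". The Randomization section adds "The therapist will sequentially open the envelopes and allocate participants accordingly".
- Patients: "The patients will not know the group to which they belong before the intervention".

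On measurement, Outcome Measurements states "Two self-report tools and two detectors will be used to measure the outcomes". The self-report tools are the VAS and the NDI, which are the two primary outcomes. The detectors measure cervical mobility and muscle properties, which are secondary.

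The Limitations section deals with blinding in one clause: "the inability to blind therapists to treatment allocation may have introduced performance bias". It does not mention participants.

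**The concern.** A reader who meets the term double-blind will normally take it that participants do not know their treatment, and will judge the risk of bias in self-reported pain and disability accordingly. The article gives the term no other definition, and its Blinding section describes something different.

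The primary hypothesis, in the Introduction, is that the combination reduces pain and disability more than either therapy alone. That comparison rests entirely on VAS and NDI. A participant who gets both therapies in a session twice as long may expect more relief and report more. If so, part of an observed advantage would be expectation, and the label would discourage readers from considering it.

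The question is not remote. The Discussion already reports interim VAS reductions of 42% in the combined group against 28% (tuina) and 31% (PNF), gaps of 14 and 11 percentage points. The Conclusion already speaks of possibly superior short-term pain relief.

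**Working it through.** The plan states no figure on this point, so the check compares its sections.

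**1. Who is blinded during treatment?**
- Therapists: no. They hold the allocation (Blinding), open the envelopes (Randomization), and are acknowledged as impossible to blind (Limitations).
- Participants: not on the list of blinded roles. The only statement about them concerns the time before the intervention. That is concealment up to the start of treatment, not blinding through it.
- Outcome assessors, data managers and statistician: yes (Blinding, Data Collection and Monitoring, Statistical Analysis).

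Neither party to the treatment is described as blinded while it is given.

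**2. Can participants tell their arm?** No section says so; this is an inference from the Intervention sections.
- PNF, about 30 minutes: therapist-assisted stretching, then contractions on instruction against resistance.
- Tuina, 30 minutes: kneading, acupoint work and neck manipulation by the therapist.
- Combined: both in sequence, about 60 minutes.

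No sham, attention control or matching of session time is described. Ethical Considerations says that consent outlines the study procedures. Recognition is therefore very likely.

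**3. What does assessor blinding protect?**
- VAS: patients are asked for their own worst pain, recorded as a whole number from 0 to 10. NDI: a self-report tool. A blinded interviewer limits prompting and recording bias but cannot mask the person who supplies the score.
- MyotonPRO: the tester does not know the grouping, so blinding works as intended.
- Cervical mobility: the device reading is protected from the assessor's knowledge, although the movement itself is made by the participant.
- Data entry and analysis: protected.

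**4. What could a bias do? (illustration only)** Inputs from Sample Size Calculation: planned VAS difference 0.135, SD 0.12, at least 20 evaluable per arm. Assumptions: no true effect, difference and SD on the same scale, and a reporting shift b in the combined arm equal to 10%, 25% or 50% of 0.135. The documents give no value for b.

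For one two-sided, two-arm t test, the noncentrality is λ = (b / SD) × √(n/2), with df = 2(20 − 1) = 38 and √(20/2) = 3.162. The false-positive rate is P(|T| > critical t) under the noncentral t distribution.

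| Shift b | b / 0.12 | λ | False positives at 0.05 | At 0.05/3 (Bonferroni, three pairs) |
|---|---|---|---|---|
| 0 | 0 | 0 | 5% | 1.7% |
| 0.0135 (10%) | 0.1125 | 0.36 | 6% | 2% |
| 0.03375 (25%) | 0.281 | 0.89 | 14% | 6% |
| 0.0675 (50%) | 0.5625 | 1.78 | 41% | 25% |

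Only ratios enter, so it is not necessary to decide whether 13.5% means 1.35 points on the 0–10 scale or a percentage of baseline, provided that difference and SD share one scale.

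**The case against.** The strongest defence is that physical therapies of this kind cannot be masked, that the article says openly who is blinded, and that self-report, unequal session length and therapist unblinding are all disclosed. Double-blind might then be read as shorthand for assessors and analysts. The first part is true, and is a reason not to use the label. The shorthand reading has no support in the text, and disclosure in one section does not correct a label in the abstract and in Study Design.

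Other parts of the defence stand, and they limit what may be concluded:

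- A reader might infer that the trial has no protection from bias. The documents do not support that. Assessors, the MyotonPRO tester, the data administrators and the statisticians are all described as blinded. The gap concerns the self-reported primary outcomes.
- A reader might treat participant recognition as a stated fact, or infer that a combination advantage would be due to expectation. Recognition is a strong inference only. The direction of any bias is less certain still: all arms are active, and the article does not say what participants are told about the hypothesis.
- A reader might take the illustrative percentages as estimates. The shifts behind them are assumed.
- A reader might conclude that the registry entry is also wrong. Its content is not shown.
- Unequal session time is not a blinding error in itself. It is disclosed, and the combination question is asked openly. It matters here because it makes the arms easier to tell apart and limits what a combination advantage can be attributed to.

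**Conclusion.** The point holds as an internal inconsistency. The abstract and Study Design claim a property that the Blinding section does not provide: neither participants nor therapists are described as blinded during treatment. Because VAS and NDI are self-reported, assessor blinding does not remove expectation bias from the primary comparison. The Limitations admit only the therapist half.

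Both primary outcomes are affected. The size and direction of any bias cannot be derived from the documents; the calculation shows only that a modest assumed shift would matter with about 20 participants per arm. The conclusion rests on one inference, that participants can tell openly different treatments apart when no sham is described. The correction should be made before the primary results, planned for December 2025, are reported.

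**What to change.** 1. In the abstract's Methods paragraph and in Study Design, replace the label with: *outcome-assessor-, data-manager- and statistician-blinded; participants and therapists not blinded during treatment*. Make the same change in the registry if its entry carries the same label.
2. In Limitations, add that participants' awareness of their treatment may bias the self-reported VAS and NDI scores.
3. State, in the protocol and in the report, that a combination advantage on VAS or NDI applies to the 60-minute package as delivered and cannot be separated from expectation.

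No change to treatments, sample size, outcomes or analysis is needed. The cost is wording, and a blinding label less favourable than the present one.

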#### Sample Size Calculation

The sample size was calculated using Granmo calculator v.7.12, based on a three-arm parallel-group design and ANOVA for means (SDs). The primary assumption was that the minimum clinically important difference (MCID) according to the VAS score is 13.5% (0.135). This value was derived from a previous NCNP study [27] and represents the minimum pain reduction considered meaningful by patients and clinicians.

The statistical parameters are as follows: alpha risk (type I error): 5% (two-sided); beta risk (type II error): 10% (power=90%); SD of mean VAS scores: estimated as 12% (0.12) based on a pilot study ([name], unpublished data, 2022).

The initial sample size was calculated as 45 participants (n=15, 33.3%, per group) to detect the specified MCID under ideal conditions (no dropouts). To make adjustments for follow-up losses, we anticipated an 8% dropout rate (based on similar rehabilitation trials [8]), so the final sample size was increased to 69 participants (n=23, 33.3%, per group) to ensure at least 20 evaluable patients per group after attrition.

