## Results

As of the data cutoff date (May 26, 2025), 43 participants were enrolled and randomly assigned to the three treatment groups (PNF group: n=14, 32.6%; tuina group: n=15, 34.9%; combined group: n=14, 32.5%), with recruitment initiated on April 1, 2025, via hospital outpatient clinics (n=45, 65.2%) and online posting (n=24, 34.8%). All enrolled participants have initiated treatment, with an average adherence rate of 92% (measured using session attendance records), and no withdrawals have occurred due to AEs or treatment dissatisfaction. The short-term follow-up (end of intervention) for the first cohort was completed on July 30, 2025, with long-term follow-up (1 month postintervention) to be completed by August 31, 2025. The final analysis is projected to include data of all 69 participants by October 2025, with primary results planned for publication in December 2025.

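### Study Design says 102 patients will be randomised, while every other section says 69 (23 per arm), and nothing explains the 102

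*Protocol article*

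**What the plan says.** The protocol article gives two numbers to be randomised.

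- **Study Design:** "A total of 102 eligible patients with NCNP will be recruited and then randomly assigned" to three arms at 1:1:1.
- **Randomization:** the three groups are filled "with 23 patients in each group".
- **Sample Size Calculation:** 45 patients (15 per arm) before losses; then, allowing for 8% dropout, "the final sample size was increased to 69 participants (n=23, 33.3%, per group"), with the aim of at least 20 evaluable per arm.
- **Abstract and Results:** "The final analysis is projected to include data of all 69 participants by October 2025".
- **Limitations:** "the sample size (N=69) may lack sensitivity".

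Three other statements bear on the point. Results reports that at the cutoff of 26 May 2025 "43 participants were enrolled and randomly assigned to the three treatment groups", having recruited "via hospital outpatient clinics (n=45, 65.2%) and online posting (n=24, 34.8"%). The Discussion summary reports an interim analysis of VAS by arm: reductions of 42% (combined), 28% (tuina) and 31% (PNF), with the combined arm described as significantly better. Statistical Analysis sets significance at P<.05 and mentions no adjustment for an interim look.

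**The concern.** The number randomised fixes when the final test is done. The 102 cannot be read as a screening figure, because the sentence calls these patients eligible and says they are then randomised. Both numbers are written out in full, so condensing a longer protocol into an article does not explain the difference.

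In a trial with no data yet, this would be an editorial slip. Here recruitment was under way, by-arm results had been seen, and the published plan carried two figures. If enrolment ended anywhere other than 69, the team could not show from this document that the stopping point was set independently of the results.

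**Working it through.** **1. Size of the contradiction.** 102/3 = 34 per arm and 69/3 = 23 per arm. 102 − 69 = 33 patients, and 33/69 = 48%. The 43 already randomised are 43/69 = 62% of one target and 43/102 = 42% of the other.

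**2. Can either figure be reproduced?** Inputs from Sample Size Calculation: difference 0.135, SD 0.12, two-sided alpha 5%, power 90%, dropout 8%.

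- *The plan's 45.* Pairwise normal approximation: n = 2(1.960 + 1.282)² × 0.12²/0.135² = 16.6, so 17 per arm and 51 in total. At 15 per arm the power is 86.9%. The 45 is close but is not reproduced.
- *The plan's 69.* 45/0.92 = 48.9, so 49 (or 15/0.92 = 16.3, so 17 per arm and 51). Going from 15 to 23 per arm would imply 1 − 15/23 = 35% dropout, not 8%. The aim of 20 evaluable needs 20/0.92 = 21.7, so 22 per arm and 66. Since 23 × 0.92 = 21.2, 69 meets that aim, but it does not follow from 45 and 8%.
- *The 102.* The table covers the natural variants at 90% power, two-sided.

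| Method | Per arm | Total | Total with 8% dropout |
|---|---|---|---|
| Pairwise, unadjusted | 17 | 51 | 57 |
| Pairwise, Bonferroni for 3 | 22 | 66 | 72 |
| One-way ANOVA, equally spaced means | 22 | 66 | 72 |

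None comes near 102. From 15 to 34 per arm would imply 1 − 15/34 = 56% dropout.

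**3. Does power favour 102?** With means equally spaced over a range of 0.135 and no losses, ANOVA power is 92.6% at 23 per arm and 98.8% at 34. On the plan's own assumptions, 69 already reaches the 90% target before losses. With 21 evaluable per arm it is 90.0%.

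**4. Illustration of what rests on the target.** Suppose a two-sided 5% test at 69 and, if not significant, another at 102, with no adjustment. Under the null the two test statistics are bivariate normal with correlation √(69/102) = 0.822. The chance that at least one exceeds 1.96 in absolute value is 7.7%.

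Adding an earlier unadjusted test requires an assumed number, because the interim n is not given. A look at 43, the number enrolled at the cutoff, gives 10.2%. A look at 30 gives 10.9% and at 20 gives 11.4%. Most of the rise above 7.7% comes from the interim look itself, not from the 102.

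**5. Recruitment sources.** 45 + 24 = 69, with 45/69 = 65.2% and 24/69 = 34.8%. The same sentence in Results reports 43 enrolled, so it mixes current enrolment with the planned total.

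**The case against.** The strongest reply is that the plan does fix its sample size. The section whose job is to set it calls 69 final, Randomization allocates 23 per arm, and the Abstract and Results commit the final analysis to 69 by October 2025. One unexplained 102 in an overview paragraph looks like a leftover. This stands. A reader might infer that the trial has no fixed sample size or stopping point; the documents do not support that.

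A reader might also infer that the sponsor plans to test at 69 and continue to 102, or that the error rate is already inflated. Nothing describes such a plan, and only one by-arm look is reported. The 7.7% describes hypothetical conduct. The 10.2% further assumes an interim test at 43, although some of the 43 enrolled between 1 April and 26 May could not have had a week-4 VAS by the cutoff. An analysis plan that is not shown might also deal with the interim look.

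Finally, the recruitment-source mismatch is a separate reporting error, and its total of 69 agrees with the other sections. That is also fair. None of this removes the contradiction: 102 remains in the text as the number to be randomised, with no explanation.

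**Conclusion.** The point holds as an internal contradiction in a core design figure: 102 (34 per arm) against 69 (23 per arm), a gap of 33 patients or 48% of 69. The text gives 69 far more support, and 102 is not reached by any sample-size variant tried on the plan's inputs. That makes a leftover likely, but the document does not say so.

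It should be settled before the final analysis, because by-arm results have been reported and no adjustment for looks is stated. The type I error figures show why the target matters; they do not show inflation that has occurred. They assume unadjusted two-sided 5% tests at each look and, for 10.2%, an interim n of 43.

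Separately, 69 is asserted more than derived, since 8% dropout takes 45 only to about 49.

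**What to change.** 1. In Study Design, replace 102 with the target used elsewhere (69, 23 per arm). If another target is intended, give its derivation and the date it was adopted, and carry it through every section. Either way, say where 102 came from.
2. State that enrolment stops at that number regardless of by-arm results, and that it was not chosen after seeing them.
3. Restate the basis for 69 in Sample Size Calculation, since 45 with 8% dropout does not give it.
4. In Results, correct the recruitment-source counts to the 43 enrolled, or label them as counts for the 69.

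The cost is a short correction, with notice to the steering and ethics committees as Quality Control already requires, and a check that the registry entry agrees. No extra patients are needed.
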